**FIGURE 1 F1:**
[figure not shown]
Flowchart of active exergame intervention (Hopewell et al., 2025). EE + ME Group: Exergame-based training plus multicomponent exercise group; ME Group: Multicomponent exercise group.

### Recruitment of participants

3.4

All individuals belonging to SENAMA day center will be invited to participate. Research support staff will conduct recruitment in person. To be eligible for participation, individuals must meet the following inclusion criteria: (i) both sexes eligible; (ii) aged ≥60 years; (iii) attendees of SENAMA day centers (senior care centers) in the Metropolitan Region of Santiago, Chile; (iv) Short Mini-Mental State Examination (MMSE-S) score >14 (Jiménez et al., 2017); (v) Functional independence measure (FIM), Index score >60 (indicating moderate to good functional independence) (Paolinelli et al., 2001); (vi) no self-reported medical contraindications for physical exercise and; (v) ability to walk independently (with or without cane). Exclusion criteria: (i) recent bone fractures or acute myocardial infarction; (ii) severe cardiovascular or respiratory conditions; (iii) uncontrolled hypertension or diabetes mellitus; (iv) cognitive or sensory impairments that limit instruction comprehension; (v) participation in other exercise programs during the study period and; (vi) inability to attend at least 80% of the intervention sessions (see Figure 1).

### Randomization

3.5

The sample was selected from among those attending the SENAMA day center, reaching a size of 52 participants. The selection was randomized among those who met the inclusion and exclusion criteria. Participants were selected according to predefined inclusion and exclusion criteria. Inclusion criteria comprised adults aged 60 years or older of both sexes, attending SENAMA day centers in the Metropolitan Region of Santiago, Chile, with a Mini-Mental State Examination (MMSE) score greater than 14 and a Barthel Index score above 60, indicating moderate to good functional independence. Participants were required to walk independently (with or without assistive devices), report no medical contraindications for physical exercise, and provide written informed consent. Exclusion criteria included recent bone fractures or acute myocardial infarction, severe cardiovascular or respiratory conditions, uncontrolled hypertension or diabetes mellitus, cognitive or sensory impairments limiting instruction comprehension, concurrent participation in other exercise programs, or inability to attend at least 80% of intervention sessions. Participants were randomized by research staff using a computer-generated sequence and concealed allocation to one of two groups (Rubenstein, 2006): the exergame-based training plus multicomponent exercise group (EE + ME group), which will receive an exergame-based program combined with multicomponent exercise, or (Pijnappels et al., 2008) the multicomponent exercise group alone (ME group), which will receive multicomponent exercise. A computer-generated simple randomization sequence stratified by gender, age, and falls risk was used to balance the groups by sex, age, ranges, and falls risk index (RRI) in both groups. The randomization sequence was concealed using sealed, opaque, sequentially numbered envelopes to ensure allocation concealment (see Figure 1).

### Procedure

3.6

Primary outcomes (risk of falls, functional independence, dynamic and static balance, center of pressure (CoP) and cardiorespiratory fitness) and secondary outcomes (body composition, upper limb strength, lower limb strength, lower limb quality muscle, quality of life and pain intensity and interference) will be assessed face-to-face 2 weeks prior to the initiation of the intervention in both groups (see Figure 2). One week prior to the intervention, there will be two induction sessions on the proper use of sports equipment and exergame use.

**FIGURE 2 F2:**
[figure not shown]
Study design showing pre-and post-intervention assessments and allocation of participants to two groups (multicomponent exercise with or without exergame-based training) during a 12-week protocol.

At the beginning of the interventions, all participants will receive an adverse symptom briefing and will be trained with the Rating of Perceived Exertion (RPE) with modified Borg Scale (Borg, 1982) to report their perception before, during and at the end of the sessions.

Throughout the 12-week intervention period, participants will be encouraged to maintain the same levels of physical activity and caloric intake as before participating in the study. Participants should report any changes in physical activity levels or nutritional intake to the physiotherapist delivering the exercise sessions. The physiotherapist will record their observations on the attendance record.

A post-intervention assessment will be conducted after the last week of the 12-week program (see Figure 2). All data collection will be carried out in a face-to-face meeting with participants at SENAMA day center and in the physiology laboratory of the Silva Henríquez Catholic University. Technical staff will be trained to ensure an unbiased procedure. Measurements will be taken individually in a place with optimal conditions of privacy, temperature, and humidity. Evaluations will be conducted by healthcare professionals. The person evaluating will be different from the person performing the interventions.

### Interventions

3.7

Exercise sessions will be held at the SENAMA day center. Regardless of the group (multicomponent exercise or multicomponent exercise plus active exergames), each session will consist of a warm-up activity (5–10 min), a main exercise activity (50 min) and a cool-down activity (5–10 min) following the guidelines of the Vivifrail multicomponent exercise program (Norton et al., 2010). Exercise intensity will be monitored based on RPE on the Borg scale modified (Borg, 1982) and vital sign parameters such as blood pressure, heart rate and saturation will be assessed before, during and after each exercise session according to the American College of Sports Medicine (ACSM) guidelines (ACSM’s, 2010), as explained below. Warm-up and cool-down activities will include stretching and walking in place (4≤RPE≤5 and 40 < 55% of heart rate reserve (HRR), while the main exercise activity will consist of strength, endurance, and balance (falls avoidance) exercises performed with dumbbells, color-coded resistance bands (Thera-Band*®*; Hygienic Corp.) Ferretti et al., 2020, and a chair (4 < RPE ≤ 6 and 55 < 70% HRR) (see Figure 3).

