**FIGURE 3 F3:**
[figure not shown]
Schematic representation of the progression in the multicomponent exercise program based on heart rate reserve (HRR), and the incremental intensity of exergame training using Nintendo Switch® Ring Fit Adventure, with more complex sets introduced as the intervention months advance.

To ensure safety and compliance, physical training will be supervised by a healthcare professional (physiotherapist) previously trained in the use of exergames. The physiotherapist will provide personalized instructions to each participant based on the modified Borg scale target and HRR depending on exercise progression. Each group will be assigned to physiotherapist with the corresponding protocol. The exergames-based training group plus multicomponent exercise will have a 55-inch television to ensure that Exergames can be viewed. During each game, participants will be required to carefully follow the instructions of a virtual trainer and control an avatar while simultaneously receiving visual, auditory, and tactile feedback. The physiotherapist will have a safe exercise protocol (for adverse events and side effects of exercise). A detailed report of the elements of the intervention is delivered through the TiDIER checklist (template for intervention description and replication) (Supplementary Table 2) (Hoffmann et al., 2014).

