#### Exergame-based training plus multicomponent exercise group (EE + ME group)

3.7.1

The video game-based training intervention will be carried out individually. The session will have a warm-up activity (5 min), main exercise activity divided into block 1 (ME) and 2 (EE) will last for 50 min, and cool-down activity (10 min), following the guidelines of a multicomponent exercise program and defined exergame use protocol. Exercise intensity will be monitored on the modified Borg scale. Warm-up and cool-down activities will include stretching, joint mobility and walking in place (4 < RPE ≤ 5 and 40 < 55% of HRR), while the main activity, in block 1, will consist of four exercise sub-blocks of 7.5 min each (strength, aerobic, balance and flexibility sub-blocks) performed with dumbbells, color-coded resistance bands (Thera-Band; Hygenic Corp.) and a chair (6<RPE≤7 and 55 < 60% of HRR in the first month and with its subsequent progression) (see Figure 3). Following the multicomponent exercise, a 5-min break will be given for hydration and continue with block 2 with Exergames (see Figure 4).

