#### Multicomponent exercise group (ME group)

3.7.2

The intervention will be conducted in a group. Each session will have a warm-up activity (5 min), main exercise activity (50 min), following the guidelines of a multicomponent exercise program. Exercise intensity will be monitored according to the modified Borg scale. Warm-up and cool-down activities will include stretching, joint mobility and walking in place (four to five RPE and 40 < 55% of HRR), while the main activity will consist of four exercise blocks of 12.5 min each (strength, aerobic, balance and flexibility sub-block) performed with dumbbells, color-coded resistance bands (Thera-Band®; Hygenic Corp.) and a chair (6 < RPE ≤ 7 and 55 < 60% RHR in the first month and with its subsequent progression) (see Figure 3). Finally, the session will culminate with a cool down (10 min).

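### The perceived-effort (RPE) target for the main exercise contradicts itself: the general section and both arm sections give month-1 bands that share no value

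*Protocol article*

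**What the plan says.** Section 3.7 (Interventions) describes the session for both arms: "Regardless of the group (multicomponent exercise or multicomponent exercise plus active exergames), each session will consist of a warm-up activity". It names the scale, "Exercise intensity will be monitored based on RPE on the Borg scale modified", and sets the main activity (strength, endurance and balance work with dumbbells, resistance bands and a chair) at "4 < RPE ≤ 6 and 55 < 70% HRR".

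Section 3.7.1 (EE + ME group) gives block 1 of the main activity, with the same equipment and the modified Borg scale, as "6<RPE≤7 and 55 < 60% of HRR in the first month and with its subsequent progression". Section 3.7.2 (ME group) gives "6 < RPE ≤ 7 and 55 < 60% RHR in the first month and with its subsequent progression". Both refer to Figure 3 for the progression.

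These bands are used in delivery. The text after the Figure 3 caption says that the physiotherapist gives "personalized instructions to each participant based on the modified Borg scale target and HRR depending on exercise progression".

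**The concern.** A general section and its arm-specific sections should nest: the starting level in each arm should lie inside the range stated for the programme. For perceived effort it does not. The month-1 band in both arms begins exactly where the general band ends.

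Two things are at stake. First, RPE is one of the two quantities from which the physiotherapist instructs each participant. The participants are aged 60 or over, and section 3.2 says that the centre gives access to people who are frail. A participant at RPE 7 in month 1 is on target by the arm section and above the limit by the general section. Second, adherence to the prescribed intensity cannot be judged, or the intervention replicated, while the document states two targets that exclude each other.

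**Working it through.** No sample-size or error-rate formula applies. The check compares intervals.

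**Inputs for the main activity**

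| Section | Applies to | RPE | Heart-rate band |
|---|---|---|---|
| 3.7 | both groups | (4, 6] | 55 to 70% HRR |
| 3.7.1 | EE + ME, block 1, month 1 | (6, 7] | 55 to 60% HRR |
| 3.7.2 | ME, month 1 | (6, 7] | 55 to 60%, printed RHR |

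**RPE.** (4, 6] ∩ (6, 7] is empty. In whole scores, section 3.7 allows {5, 6} and the arm sections allow {7}. A grid in steps of 0.1 also gives no common value. If the strict lower bound in the arm sections were read as 6 or more, the bands would meet at the single value 6 and nowhere else.

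**Heart rate.** 55–60% is contained in 55–70%, so there is no conflict. The month-1 band is the lower part of the general one, as a starting step would be. The lower part of the heart-rate range is thus paired with an RPE band above the general RPE range, which suggests that at least one RPE band is misprinted.

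**Between arms.** Sections 3.7.1 and 3.7.2 print the same month-1 RPE band and the same percentages. The conflict is between the general section and both arm sections, not between the arms.

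**Extent in time.** Two sessions a week for 12 weeks is 2 × 12 = 24 sessions. Taking a month as 4 weeks, month 1 is 2 × 4 = 8 sessions. Later RPE values are not printed in the text.

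**Extent within the session.** In EE + ME the printed band covers block 1, 4 × 7.5 = 30 of the 50 minutes; the text gives no separate RPE band for the 20-minute exergame block. In ME it covers 4 × 12.5 = 50 minutes.

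**Could progression explain it?** If section 3.7 covers the whole programme, as its wider heart-rate range suggests, month 1 should lie inside its RPE band, and it does not. Upward progression would widen the gap. A later fall in RPE would still leave month 1 in conflict.

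**The case against.** The strongest reply is that the damage is limited. Section 3.7 is an overview. Each physiotherapist is assigned to one group with that group's protocol, and the two arm sections agree on month 1. The Figure 3 caption describes the progression of the multicomponent programme in terms of heart-rate reserve, and that measure is consistent across the three sections. Sessions are supervised, with vital signs taken before, during and after, and there is a protocol for adverse events. All of this stands. It limits the consequences but does not make the two RPE bands compatible.

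A reader might infer more than the document supports:

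- **That the arms will train at different intensities, which would confound the comparison.** The printed month-1 bands are identical in the two arms. A difference would arise only if one physiotherapist followed section 3.7 and the other an arm section, and nothing in the document says so.
- **That all 24 sessions are affected.** This assumes that RPE never returns to the general band after month 1. Figure 3 is not shown here, so that cannot be checked.
- **That the whole intensity prescription is contradictory.** The heart-rate bands nest.
- **That RHR in section 3.7.2 sets a different heart-rate reference.** The same sentence uses HRR for the warm-up, and 55–60% of a resting heart rate would lie below rest. It is evidently a transposition.

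That Figure 3 is not shown does not weaken the point. No figure can reconcile two printed bands that exclude each other.

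**Conclusion.** The point holds for perceived effort. Section 3.7 and sections 3.7.1 and 3.7.2 set month-1 RPE bands with no common value, on the same scale and for the same activity. The contradiction is demonstrated for about 8 of 24 sessions in each arm, and in EE + ME for block 1 only.

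This rests on reading section 3.7 as covering month 1 in both groups, which its wording supports, and on counting a month as 4 weeks. A non-strict lower bound in the arm sections would leave one shared value, 6.

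The consequence is an undefined effort target and no agreed standard for judging adherence to it. By itself the contradiction does not affect the randomised contrast, the outcomes or the analysis. The document does not show which band is intended, and that is not for a statistical review to decide.

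**What to change.** Reconcile the RPE band for the main activity across sections 3.7, 3.7.1, 3.7.2 and Figure 3, so that each phase of the programme has one stated range. The trial team decides the values. In the same amendment, replace RHR in section 3.7.2 with the HRR term used elsewhere.

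Then summarise by arm and phase the RPE and heart rate already taken at each session, against the reconciled ranges. This fidelity check would also show whether the arms were in fact trained at similar effort.

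The cost is a wording amendment and a short briefing of the physiotherapists, with no new measurement. One caution: section 3.5 describes selection and randomisation in the past tense. If training has already begun, the amendment cannot establish which band was delivered. The session records should then be used to describe what was done, and the report should state which target was in force.

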**FIGURE 3 F3:**
[figure not shown]
Schematic representation of the progression in the multicomponent exercise program based on heart rate reserve (HRR), and the incremental intensity of exergame training using Nintendo Switch® Ring Fit Adventure, with more complex sets introduced as the intervention months advance.

To ensure safety and compliance, physical training will be supervised by a healthcare professional (physiotherapist) previously trained in the use of exergames. The physiotherapist will provide personalized instructions to each participant based on the modified Borg scale target and HRR depending on exercise progression. Each group will be assigned to physiotherapist with the corresponding protocol. The exergames-based training group plus multicomponent exercise will have a 55-inch television to ensure that Exergames can be viewed. During each game, participants will be required to carefully follow the instructions of a virtual trainer and control an avatar while simultaneously receiving visual, auditory, and tactile feedback. The physiotherapist will have a safe exercise protocol (for adverse events and side effects of exercise). A detailed report of the elements of the intervention is delivered through the TiDIER checklist (template for intervention description and replication) (Supplementary Table 2) (Hoffmann et al., 2014).

#### Exergame-based training plus multicomponent exercise group (EE + ME group)

3.7.1

The video game-based training intervention will be carried out individually. The session will have a warm-up activity (5 min), main exercise activity divided into block 1 (ME) and 2 (EE) will last for 50 min, and cool-down activity (10 min), following the guidelines of a multicomponent exercise program and defined exergame use protocol. Exercise intensity will be monitored on the modified Borg scale. Warm-up and cool-down activities will include stretching, joint mobility and walking in place (4 < RPE ≤ 5 and 40 < 55% of HRR), while the main activity, in block 1, will consist of four exercise sub-blocks of 7.5 min each (strength, aerobic, balance and flexibility sub-blocks) performed with dumbbells, color-coded resistance bands (Thera-Band; Hygenic Corp.) and a chair (6<RPE≤7 and 55 < 60% of HRR in the first month and with its subsequent progression) (see Figure 3). Following the multicomponent exercise, a 5-min break will be given for hydration and continue with block 2 with Exergames (see Figure 4).

**FIGURE 4 F4:**
[figure not shown]
Example of structure and components of Session 1 for EE-ME group.

The exergame-based training session will last 20 min thus ensuring an equivalent exercise time in both groups (50 min per session) where participants will perform the set defined by the physiotherapist, for each week and month, according to the progression (see Figure 3). They included a series of analytical exercises, yoga postures, and playful physical activities from the game Ring Fit Adventure (Nintendo Switch®). The exergame protocol has a variety of sets (see Table 1), which will be adapted according to the progression of the exercise. The list of individual exergame activities and their description is provided in Supplementary Tables 3a b
*, respectively* (Guede-Rojas et al., 2025). Finally, the session will culminate with a cool down (10 min).

**TABLE 1 T1:** Risk of fall and functional capacity, physiological, and self-reported outcomes.

Domain	Outcome	Measurement tool/Test	Units/Scale
Risk of fall and functional capacity	Fall risk	Downton Fall Risk Index (DFRI)	0–11 points (≥3 = high risk)
	Dynamic balance	Timed Up and Go (TUG) test	Time (s), best of 3 trials
	Static balance	Single-Leg Stance Test	Time (s), best of 3 trials
		Posturography (Smart Balance Hur® Labs BTG4-F)	Romberg quotient; C90 area (cm²)
	Cardiorespiratory fitness	2-Minute Walk Test	Number of steps in 2 min
Physiological	Upper-limb strength	Handgrip Strength Test (BASELINE® dynamometer)	Force (kg), best of 2 trials
	Lower-limb strength	Five-Repetition Sit-to-Stand Test	Time (s)
	Muscle quality	Ultrasound (quadriceps, tibialis anterior) analyzed with Image J®	Muscle thickness (mm) and echogenicity (0–255 a.u.).
	Body composition	Bioelectrical Impedance Analysis (InBody 270®)	Skeletal mass, segmental muscle mass and fat mass (kg and %).
Self-reported	Functional independence	Functional Independence Measure (FIM)	18 items, 7-point scale (1 = dependence – 7 = independence)
	Quality of life	36-Item Short Form Health Survey (SF-36, Spanish version)	0–100 points (higher = better)
	Physical activity	International Physical Activity Questionnaire (IPAQ)	MET-min per week
	Pain intensity & interference	Brief Pain Inventory – Short Form (BPI-SF)	0–10 numeric scales (average score)

#### Multicomponent exercise group (ME group)

3.7.2

The intervention will be conducted in a group. Each session will have a warm-up activity (5 min), main exercise activity (50 min), following the guidelines of a multicomponent exercise program. Exercise intensity will be monitored according to the modified Borg scale. Warm-up and cool-down activities will include stretching, joint mobility and walking in place (four to five RPE and 40 < 55% of HRR), while the main activity will consist of four exercise blocks of 12.5 min each (strength, aerobic, balance and flexibility sub-block) performed with dumbbells, color-coded resistance bands (Thera-Band®; Hygenic Corp.) and a chair (6 < RPE ≤ 7 and 55 < 60% RHR in the first month and with its subsequent progression) (see Figure 3). Finally, the session will culminate with a cool down (10 min).

### Outcome measures

3.8

Physical fitness, functional status and quality of life will be assessed before and after the interventions. All measurements will be performed by two physiotherapists who are not familiar with the group assignment scheme, which will ensure an unbiased procedure. In addition, all measurements will be performed in the physiology laboratory of Católica Silva Henríquez University and will be obtained individually in an environment with optimal conditions of privacy, temperature and humidity. Data will be recorded on standardized forms and entered into a secure access database containing quality control checks (e.g., range checks and missing data notifications). The primary outcomes were selected based on studies that analyzed core outcome sets recommended for evaluating the effectiveness of interventions in people at risk of falls, as reported in the COMET initiative. This approach ensures that the selected outcomes are clinically meaningful, internationally comparable, and aligned with best practice standards (O’Malley et al., 2023; Lamb et al., 2005; Copsey et al., 2016) Thus, will include risk of fall, functional independence, measures of static and dynamic balance, center of pressure, cardiorespiratory fitness; while secondary outcomes will assess body composition, upper and lower limb strength, muscle quality of the lower limb, physical activity level, perceived quality of life and perceived pain. The variables are summarized according to three main domains and are presented in Table 1.

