### Power calculation

3.3

The sample size was calculated as *a priori* using G*Power 3.1.9.7. Forty-six participants in total are required (23 in each group), considering α = 0.05, 1-β = 0.8, and effect size (ES) = 0.8 (Lower limb strength based on the results of a previous study) Considering the possibility of dropouts percentage, six participants were added (see Figure 1).

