#### Primary outcomes

3.8.1

Risk of fall: Falls risk will be evaluated using the Downton Fall Risk Index (DFRI), a five-item composite score based on prior falls, medication, sensory deficits, mental state, and mobility. A score of less than three points means low risk of fall, and a total score above three points indicates a high risk of fall (Downton index, 2016).

Balance: Dynamic balance will be measured with the Timed Up and Go (TUG) test, which evaluates the time in seconds that a participant takes to rise from a chair, walk 3 m, turn, return, and sit down again (Mancilla et al., 2015) The test will be assessed three times, and the best attempt will be recorded. While static balance will be measured thought the single-Leg Stance Test, where participants must maintain balance on one leg for at least 5 s (Mancilla et al., 2015) The test will be assessed three times, and the best attempt will be recorded.

Posturography: Romberg quotient and C90 area will be measured (Smart Balance Hur® Labs model BTG4-F, Kokkola, Finland). Posturography records center of pressure displacement while standing on a stable platform (Furman, 1994; Visser et al., 2008). Participants must maintain a bipedal posture with feet shoulder width apart, hands hanging at the sides of the body and head facing forward. They must also follow the evaluator’s instruction, either eyes open (condition 1) or closed (condition 2). The foot resting points on the platform are marked to ensure repeatability.

Functional independence: this outcome will be measured with Functional Independence Measure (FIM) scale, it consists of 18 items that assess both motor and cognitive skills, and is scored on a 7-level scale, where one indicates total dependence and seven complete independence (Paolinelli et al., 2001).

Cardiorespiratory fitness: Aerobic capacity will be measured by the 2-Minute Walk Test, which measures the total distance (in meters) covered at a self-selected walking pace within 2 min on a flat surface, a full step is defined as a step performed by raising the knee to a height corresponding to the midpoint between the patella and the iliac crest (Guralnik et al., 1994).

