### Statistical analysis

3.10

Missing data will be handled by intention-to-treat analysis (multiple imputation method) [65]. The data will be analyzed using the intention-to-treat (ITT) strategy (Ahn and Kang, 2023). The description will be made as measures of central tendency and dispersion (continuous variables) and as percentages (categorical variables). Using the Shapiro-Wilk test, the normality of the data will be verified, and a two-step approach for transforming will be applied to the non-normal variables (A Two-Step Approach for Transforming, 2004). Homoscedasticity will be analyzed using Levene’s test. A 2-way repeated measures analysis of variance (ANOVA) will be used to determine the effects of interventions. The effects of the model are the group (GE; GC), the times (Pretest; Posttest), and their interaction over time (Time x Group). The effect size (ES) will be determined using Cohen’s d (<0.2 insignificant; ≥0.2 and ≤0.49 small; ≥0.5 and ≤0.79 moderate; ≥0.8 large) (Cohen, 2004). Additionally, in clinically relevant outcomes (risk of fall), the minimum clinically important difference (MCID) will be evaluated. All analyses will be performed with SPSS® v.26 (SPSS, Inc., Chicago, IL, USA), considering p < 0.05 and GraphPad Prism® v8.

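### Seven or more unranked primary measures are all judged at p < 0.05 with no deciding outcome, and, as a separate fault, the trial is sized on a secondary outcome

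*Protocol article*

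**What the plan says.** Section 3.8 gives the primary set as "risk of fall, functional independence, measures of static and dynamic balance, center of pressure, cardiorespiratory fitness". Section 3.8.1 makes these measurable: the Downton Fall Risk Index (DFRI), Timed Up and Go (TUG), single-leg stance, Romberg quotient, C90 area, Functional Independence Measure (FIM) and the 2-minute walk. That is seven measures. Posturography is recorded with eyes open and with eyes closed, so C90 area could supply two and make eight.

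Section 3.10 plans a two-way repeated-measures ANOVA with group, time and time x group effects, and sets the level for all analyses by "considering p < 0.05". It names no deciding outcome, deciding effect, testing order or adjustment. Its one remark specific to an outcome is that a minimum clinically important difference will be evaluated for fall risk.

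Section 3.3 sizes the trial with "considering α = 0.05, 1-β = 0.8" and "effect size (ES) = 0.8", and gives the source of the effect size as "Lower limb strength based on the results of a previous study". Section 3.8 puts that outcome in the other class: "secondary outcomes will assess body composition, upper and lower limb strength". Sections 3.6 and 3.8.2 agree that it is secondary.

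**The concern.** There are two faults with different consequences.

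1. **Error rate.** With seven or more primary measures of equal standing, each at 0.05, any single positive could be reported as success on a primary outcome. The plan gives no basis for saying beforehand which pattern of results would show that the exergame programme works.
2. **Power.** The only power statement concerns a secondary outcome. A null result on TUG, DFRI or any other primary measure could not be read against a planned power, because none was planned.

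The second fault does not cause the first. Sizing on the wrong outcome leaves power unjustified but does not change the false-positive rate.

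**Working it through.** **Inputs from the article.** Level 0.05 (3.3 and 3.10); planned power 0.80 and effect size 0.8, read as Cohen's d (3.3); 23 per group required, 26 per group randomised (3.3, Abstract); seven primary measures, possibly eight (3.8.1).

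**Assumed, because the article does not say.** One two-sided time x group test per measure, which is the smallest reading of 3.10; equal correlation between the test statistics, varied from 0 to 0.9.

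**Step 1: the plan's own figure.** For a two-sided two-sample t test with d = 0.8, the degrees of freedom are 2n − 2 and the noncentrality is d√(n/2).
- n = 23: 0.8 × √11.5 = 2.71, power 75.6%.
- n = 26: 0.8 × √13 = 2.88, power 80.7%.

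So 80% power needs 26 per group (52 completers) two-sided, or 21 per group (42) one-sided. The stated 46 is neither. Section 3.3 does not give the test or its sidedness, and other test families with undocumented settings come near 46. This is a side observation. For the present point, what matters is that the calculation, right or wrong, is for lower-limb strength.

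**Step 2: error rate with independent measures.**
- Any false significant result, either direction: 1 − 0.95^7 = 0.302. With eight tests: 1 − 0.95^8 = 0.337.
- Any false result favouring the exergame arm: 1 − 0.975^7 = 0.162, against 0.025 for a single test.

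**Step 3: error rate with correlated measures.** Statistics were simulated as Z_j = √ρ·W + √(1 − ρ)·E_j, with W and E_j standard normal, in 400,000 draws. A false result in either direction is |Z_j| > 1.96 for at least one j; one favouring the exergame arm is Z_j > 1.96 for at least one j. For seven measures:

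| Correlation ρ | Either direction | Favouring exergame |
|---|---|---|
| 0 | 30.2% | 16.2% |
| 0.3 | 27.2% | 13.7% |
| 0.5 | 22.9% | 11.5% |
| 0.7 | 17.9% | 9.0% |
| 0.8 | 14.9% | 7.4% |
| 0.9 | 11.5% | 5.7% |

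With eight measures the either-direction figure is 19.0% at ρ = 0.7.

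**Step 4: what adjustment would cost.** Bonferroni over seven uses 0.05/7 = 0.00714 and is a lower bound for Holm. At d = 0.8, used only as an illustration because no effect size is given for any primary measure:

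| Per group | Unadjusted 0.05 | Bonferroni over seven |
|---|---|---|
| 23 | 75.6% | 46.5% |
| 26 | 80.7% | 53.6% |

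Keeping 80% power at 0.00714 would take 41 per group.

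**The case against.** The strongest reply is that multiplicity is commonly left to a statistical analysis plan, which is not shown, and that the p < 0.05 in 3.10 sits in a general software sentence that does not rule out adjusted p-values. That could excuse silence on method alone. It does not excuse the rest: which outcomes are primary, which outcome the sample size serves, and the level for all analyses are fixed in this document, and they do not fit together.

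A second reply is that fall risk is in effect the lead outcome, since it heads each primary list and is the one singled out for a minimum clinically important difference. The article never says that it decides the trial, and list position is not a testing order.

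Some stronger readings are tempting but not supported:

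- A reader might take 18-30% as the chance of wrongly declaring the exergame programme effective. That range counts results in both directions. In favour of the exergame arm it is about 9-16%, and would be higher only if a group or time main effect also counted as success, which the article leaves open. Nor is 18% a floor: the either-direction figure falls to about 11-15% at correlations of 0.8-0.9.
- A reader might infer from the description of DFRI as "a five-item composite score based on prior falls, medication, sensory deficits, mental state, and mobility" that it can hardly change in 12 weeks. Four of the five components are not mobility, but the article gives neither component weights nor data on responsiveness.
- A reader might infer that TUG must be the primary outcome because balance is the aim throughout. The Abstract's Objective and the primary objective restated in the Discussion do not mention balance. TUG is a reasonable candidate and no more.

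**Conclusion.** Both faults stand, separately.

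1. As written, the primary error rate is not held at 5%. Over seven measures, the chance of at least one false significant result in either direction is 30% under independence, 23% at correlation 0.5, 18% at 0.7 and about 11-15% at 0.8-0.9. In favour of the exergame arm it is about 9-16% at correlations 0.7 to 0, or 3.6 to 6.5 times the nominal 2.5%. These figures assume no true effect, one time x group test per measure and equal correlations. The exact size is uncertain, but every value examined is above nominal.
2. The stated 80% power attaches to no primary outcome. This follows from the text alone and needs no assumption.

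This should be fixed before analysis: the plan as it stands does not say what result would count as success.

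**What to change.** Before any outcome data are compared by arm, do one of the following in 3.8 and 3.10:

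- **One primary.** Name one outcome and one contrast, the time x group effect at the 12-week assessment, and make the other current primaries secondary. TUG is one candidate because it is continuous and is defined alike in 3.8.1 and Table 1. The 2-minute test is not yet usable in this way: it is in metres in 3.8.1 and in steps in Table 1. The choice is the sponsor's.
- **Several primaries.** Keep the list, state whether C90 area counts once or twice, apply Holm across all the measures, and claim effectiveness only for those that survive.

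In 3.3, either say that the power figure refers to a secondary outcome, or restate it for the chosen primary with its own assumed difference and standard deviation. The article supplies neither, so the sponsor must source them.

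**Cost.** Under the first option, fewer outcomes can carry a primary claim. Under the second, power per outcome falls: in the d = 0.8 illustration with 26 per arm, from about 81% unadjusted to a lower bound of about 54%. Either needs a protocol and registry amendment. Section 3.5 reports randomization in the past tense, although the Abstract uses the future, so the amendment should be dated and should record that it was made before outcome data were compared by arm.
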